#### Delivery of Educational Workshops

At first, the workshops will be offered in French considering that a majority of patients treated at the SJUHC CCCB are French speaking, but they will eventually be translated and offered in English. The lessons will be dispensed on a weekly basis. Weekly rotation of the 6 themed lessons and variable scheduled day and time will contribute to maximize participants’ exposure and participation. A total of 40 workshops will be offered each year for 4 years. The workshops will take place at the SJUHC CCCB in a room designed for this purpose. Participants will be invited to taste the demonstrated recipes at the end of the workshop, and printed material will be distributed, including recipes and key messages. Because the mean age of patients treated at the CCCB is 7 years old, additional food-related activities are planned for young children. A signature sheet will be used to record attendance at each session. Videotaped workshops will also be made available to participants on a secure Web platform. Posters will advertise the schedule and topics of the workshops, and the clinical team will receive reminders of the upcoming workshops so they can promote attendance.

#### Workshop Evaluation Tools and Outcome Measurement

A total of 6 self-administered post-intervention questionnaires were developed to measure short-term outcomes of the workshops, namely, perception of knowledge acquisition, behavioral intention, and satisfaction. At the end of each workshop, adults and children of 12 years and older will be asked to fill out a printed version of the lesson-specific questionnaire available in both French and English. To reduce the burden of participants, the questionnaires contain limited number of items and can be answered in a few minutes. The questionnaires have been reviewed by an expert in the field of program evaluation and were pretested with the target population to validate their comprehension and literacy [62].

These questionnaires will measure participants’ perception of knowledge acquisition based on the corresponding workshop’s key messages [63]. This measure based on the perception was preferred to a scholastic questionnaire that measures knowledge to reduce participants’ burden. Overall, 3 to 4 items are presented in the form of a statement derived from the learning objectives (key messages) and begin with “I have learned.” Participants will answer according to their degree of agreement: “I agree,” “I agree more or less,” “I don’t agree,” or “I already knew this information.” Additional questions about the intention to try the recipes at home or to use the information to adapt the child’s diet [62] are also included. Participants’ relationship with the patient (patient, parent, grandparent, etc) consists in the only sociodemographic item captured by the questionnaire. General satisfaction will be measured by asking about the intention to recommend the workshop to others and, if not, to specify why. Finally, a comment section will enquire for qualitative feedback and for suggestions to improve the curriculum.

An activity report to be filled out by the facilitators after each session has also been developed to assess fidelity to the developed curriculum, to record attendance at each session, and to document any adverse event that could have disturbed the group or compromise content transmission. Qualitative feedback from facilitators related to challenges experienced during the workshops will also be sought in the activity report. These short-term outcome data will be used for evaluating the educational workshops.

Medium-term outcomes of the workshops as a component of the nutrition program will be measured as part of the evaluation of the broader controlled study of the VIE Program. Data will be collected by research staff at the beginning, during, and at the end of the intervention for each participant in the program. They will include socio-demographic data (ethnicity and socio-economic status), clinical data (age, diagnosis, age at diagnosis, and treatment protocol), anthropometric profile (body mass index, tricipital and subscapular skinfolds, head circumference [for children <3 years old]), and biomarkers of metabolic health (fasting lipid profile, glucose, insulin, and glycated hemoglobin). Diet will be assessed by an RD using 24-hour diet recalls and food journals. Diet data will be analyzed using the software Nutrific (Department of Food Science and Nutrition, Université Laval, Montreal, Canada). Nutrient values from this application are derived from the 2010 Canadian Nutrient File. Participation in workshops will be assessed using an attendance sheet at each workshop and by questioning participants and their family, at RD follow-up visits, the workshops attended or viewed on the Web platform, and their topics. Quality of diet and anthropometric and biochemical profiles will be analyzed in relation to workshop attendance and will be compared with those of the control group who did not participate in the workshops. Qualitative data regarding usefulness of each workshop will also be collected through focus groups of workshops’ participants. They will be leaded by the research RD and will take place at the end of selected sessions for all 6 thematic workshops. Collected data will be subject to thematic analysis to better understand if attendance to specific sessions is related to participants’ success.

A logic model [64,65] has been developed describing the resources needed (inputs), the activities achieved or to be implemented, the public reached (outputs), and the expected short- and medium-term outcomes of the VIE Program educational workshops (Figure 2).

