## Methods

### Setting

We have developed a protocol for a nonrandomized controlled study. This study has been developed within the VIE (Valorization, Implication, Education) Program at the Sainte-Justine University Health Center (SJUHC) in Montreal, Canada. This research program consists of a 4-year family-oriented multidisciplinary interventional program integrating physical activity, nutrition, and psychosocial clinical and research teams. The nutritional intervention includes personalized assessment, goal setting, and counseling for behavioral changes with a registered dietitian (RD) as well as group nutrition education and cooking workshops providing complementary information. The SJUHC Institutional Review Board approved the study, and investigations will be carried out in accordance with the principles of the Declaration of Helsinki.

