### Study Protocol

#### Recruitment of Participants and Controls

From January 2018 to December 2020, parents and children newly diagnosed with cancer, treated at the SJUHC, and meeting the inclusion criteria will be offered to participate in the VIE Program. Participant recruitment will be sequential. Inclusion criteria are as follows: (1) being less than 21 years old at diagnosis, (2) being treated with radiotherapy or chemotherapy (including patients receiving hematopoietic cell transplantation), and (3) able to give an informed consent (by parents or legal tutors). Participants who are not receiving radiotherapy or chemotherapy will be excluded from the study. Patients will be followed for 4 years. On average, 140 children per year are admitted at the SJUHC’s CCCB, of which about 110 would be eligible. On the basis of earlier studies, we expect an average of 75 patients recruited per year (70.0% recruitment rate), for a total of 150 participants over 2 years. Enrolled participants and their family (parents, grandparents, etc) will be encouraged to attend the nutrition education and cooking workshops. It is to the parents’ discretion to attend workshops with or without the child, according to the child’s age, interest, and health condition. The control group will be recruited sequentially from patients diagnosed at the CCCB 3 to 4 years ago, who were not exposed to the VIE Program and who fulfill the same inclusion criteria as for the intervention group. No intervention will be offered to control participants. The measures and questions used will be the same as for the end-of-protocol intervention in the patients from the intervention group.

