## Discussion

### Development of the Intervention

With this study, we have developed a family-oriented nutrition education and cooking workshop curriculum specific to pediatric oncology. The elaboration based on scientific evidence and on years of clinical experience, combined with an 8-step validation process, are strengths and features of interest of this study [64,66]. There is a consensus on the value of including field actors and representatives of the target population in the development of lifestyle interventions. Including clinicians in the development process offers precious insight to enhance the curriculum content and ensures coherence with the medical team. In CCS overweight children, a group lifestyle intervention used interviews and focus groups with health care providers and CCS parents to adapt a curriculum previously shown to be effective in non-CCS overweight children [67].

Some authors suggested that adding a cooking component to nutrition education is a good way to enhance participants’ skills and increase application of knowledge [68,69]. In our curriculum, cooking demonstrations will allow observational learning [68] and may enhance participants’ familiarity with specific foods [70], cooking techniques, and food safety practices. Moreover, the nutrition education content will focus on practical application as several ideas to apply recommendations and tips to overcome barriers to healthy eating and home cooking will be presented. Furthermore, the developed content aims at reinforcing the messages conveyed by the clinical and research RD during individual follow-up. Therefore, the workshops may serve as a complementary intervention tool to facilitate behavioral change.

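### The medium-term control comparison estimates the effect of the whole VIE Program, not of the workshops, and should be labelled that way

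*Protocol article*

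**What the plan says.** Under Setting, the article describes the VIE Program as a "multidisciplinary interventional program integrating physical activity, nutrition, and psychosocial clinical and research teams". Its nutrition part consists of "personalized assessment, goal setting, and counseling for behavioral changes with a registered dietitian (RD) as well as group nutrition education and cooking workshops". The workshops are thus one element of one of three strands.

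Under Recruitment of Participants and Controls, the controls are earlier patients of the same centre "who were not exposed to the VIE Program and who fulfill the same inclusion criteria as for the intervention group". The section adds: "No intervention will be offered to control participants".

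Under Workshop Evaluation Tools and Outcome Measurement, the framing sentence, which refers to VIE as a whole, reads: "Medium-term outcomes of the workshops as a component of the nutrition program will be measured as part of the evaluation of the broader controlled study". The same paragraph plans to relate diet quality, anthropometric and biochemical profiles to workshop attendance. It then says that these profiles "will be compared with those of the control group who did not participate in the workshops".

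At the end of the Introduction, measuring the impact of the workshops is given as a purpose of the study protocol.

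**The concern.** The control group is identified by one thing it lacked, the workshops, when by the article's own account it lacked the whole programme. The outcomes are labelled as those of the workshops. Taken together, the two statements invite the reader to treat a VIE versus no-VIE difference as a workshop effect.

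The other components plausibly act on the same outcomes. The Discussion says of the workshops that "the developed content aims at reinforcing the messages conveyed by the clinical and research RD during individual follow-up", so individual counselling and workshops push diet in the same direction. The Introduction names physical activity alongside healthy eating as a modifiable factor for cardiometabolic risk. The Discussion also expects the workshops to be a valuable complement to the VIE lifestyle intervention. That is a statement about added value over the rest of the programme, and a comparison with patients who had none of the programme cannot support it.

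**Working it through.** There is no figure in the plan to reproduce. The total of 150 participants is a recruitment expectation (75 per year × 2 years = 150), not a power calculation for this comparison. The check is a side-by-side reading of what each group receives.

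| Component | VIE group | Control group | Source |
|---|---|---|---|
| Group workshops | Offered; attendance encouraged | No | Setting; Recruitment of Participants and Controls |
| Study dietitian assessment, goal setting, counselling | Part of the programme | No | Same |
| Physical activity component | Part of the programme | No | Same |
| Psychosocial component | Part of the programme | No | Same |
| Time of diagnosis | Newly diagnosed, January 2018 to December 2020 | Diagnosed 3 to 4 years before recruitment | Recruitment of Participants and Controls |

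All four components change together between the columns, and so does the era.

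Write the expected difference between the groups as

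Δ = W + R + B,

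where W is the contribution of the workshops, R that of the rest of VIE (including any joint action with the workshops), and B the bias from era and selection. The comparison supplies one quantity, Δ. Even with B = 0, two opposite situations give the same result:

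- workshops without effect, remainder with effect D: Δ = 0 + D = D;
- workshops with effect D, remainder without effect: Δ = D + 0 = D.

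A larger sample narrows the interval around Δ but does not split it. Nor does covariate adjustment, because within this comparison exposure to the rest of VIE coincides with group membership. Randomising patients to the whole programme or nothing would address B and leave W and R just as inseparable. The limitation that the Discussion acknowledges, the non-randomised design, is therefore a different one.

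The planned attendance analysis is a separate contrast. Within the VIE group all patients are offered the other components, so attendance is not tied to programme membership. But attendance is voluntary. The article leaves it to the parents whether to bring the child, according to age, interest and health condition, and similar factors may decide whether a family comes at all. Families who attend more may also be more engaged with the dietitian. That analysis can show an association between attendance and outcome, not a clean workshop effect.

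**The case against.** The strongest reply is that the article does not hide the wider setting. Its framing sentence calls the workshops a component of the nutrition program and places the measurement inside the broader controlled study. The controls are correctly defined, under Recruitment of Participants and Controls, by non-exposure to VIE. The attendance analysis appears in the same sentence as the control comparison. Workshop evaluation is also assigned to other data: the post-workshop questionnaires and facilitators' activity reports, which need no control group, and the focus groups.

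All of this stands, and it limits the point. A reader might infer that the plan will credit any VIE benefit to the workshops, or that it leaves workshop impact wholly unexamined. The documents support neither. No sentence sets a rule attributing the control difference to the workshops, and no test or hypothesis is stated for it. Short-term workshop evaluation has its own instruments.

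Two further cautions are fair. It cannot be said that controls had no dietitian contact: the centre has experienced clinical dietitians and the controls received standard treatment, so what they lacked is the study's counselling. And the article does not say how much of the physical activity and psychosocial components each patient receives. The point does not depend on that, since the study dietitian's counselling alone is enough to make the workshop share unidentifiable.

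The reply does not remove the mismatch. The outcomes are still labelled as those of the workshops, the comparison clause describes controls only by workshop non-participation, no sentence says that this comparison estimates the whole programme, and co-intervention is absent from the limitations in the Discussion.

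**Conclusion.** The point holds as one of labelling and interpretation. The control comparison estimates the effect of the whole VIE Program plus era and selection differences, and it can support no workshop-specific conclusion at any sample size. The share that could be misattributed ranges from none to all of the observed difference, or beyond if era and selection effects oppose it; the article gives nothing with which to narrow this.

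The conclusion rests only on the stated composition of the programme and the stated non-exposure of the controls. It needs no assumption about power, variability or effect size. It bears on what may be concluded about medium-term outcomes. It does not undermine the short-term workshop evaluation and does not call for a new design. It should be corrected before medium-term results are reported.

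**What to change.** 1. In Workshop Evaluation Tools and Outcome Measurement, describe the controls as unexposed to the VIE Program. State that the comparison with them estimates the effect of the whole programme and supports no conclusion specific to the workshops.
2. Base medium-term workshop statements only on the already planned attendance analysis within the VIE group. Adjust it for the baseline value of the outcome and for the baseline clinical and socio-demographic factors already collected (age, diagnosis, treatment protocol, ethnicity, socio-economic status), and report it as an exploratory association.
3. If dietitian visit counts are recorded, add adjustment for them as a sensitivity analysis only. The article mentions follow-up visits but does not say that they are counted. The count arises after baseline and may reflect the child's health or the family's engagement.
4. In the Discussion, add co-intervention to the limitations, separately from non-randomisation.

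The cost is a few sentences and the specification of covariates already in hand, with no change to recruitment, data collection or planned contrasts. The price is a more modest claim for the workshops.

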**Figure 2 figure2:**
[figure not shown]
Logic model of the VIE (Valorization, Implication, Education) Program educational workshops. SJUHC: Sainte-Justine University Health Center; RD: registered dietitian; CCCB: Centre de cancérologie Charles-Bruneau.

## Results

The project was funded in 2016 and enrollment will be completed in 2021. Data analysis is currently under way and the first results are expected to be submitted for publication in 2019.

## Discussion

### Development of the Intervention

With this study, we have developed a family-oriented nutrition education and cooking workshop curriculum specific to pediatric oncology. The elaboration based on scientific evidence and on years of clinical experience, combined with an 8-step validation process, are strengths and features of interest of this study [64,66]. There is a consensus on the value of including field actors and representatives of the target population in the development of lifestyle interventions. Including clinicians in the development process offers precious insight to enhance the curriculum content and ensures coherence with the medical team. In CCS overweight children, a group lifestyle intervention used interviews and focus groups with health care providers and CCS parents to adapt a curriculum previously shown to be effective in non-CCS overweight children [67].

Some authors suggested that adding a cooking component to nutrition education is a good way to enhance participants’ skills and increase application of knowledge [68,69]. In our curriculum, cooking demonstrations will allow observational learning [68] and may enhance participants’ familiarity with specific foods [70], cooking techniques, and food safety practices. Moreover, the nutrition education content will focus on practical application as several ideas to apply recommendations and tips to overcome barriers to healthy eating and home cooking will be presented. Furthermore, the developed content aims at reinforcing the messages conveyed by the clinical and research RD during individual follow-up. Therefore, the workshops may serve as a complementary intervention tool to facilitate behavioral change.

### Familial Influence on the Development of Eating Habits

The curriculum was developed based on the social-ecological model, considering that individuals’ eating behaviors are influenced by determinants of their environment [71]. Family, as part of their social environment, is one of the most influent determinants of healthy eating in children. Indeed, parents play a crucial role as they usually are responsible for food selection, serve as role models, and use parental feeding practices that impact children’s eating behaviors [72]. According to studies designed for obesity prevention or management in children, family-oriented lifestyle interventions are the most effective in noncancer and in CCS populations [15,73]. Therefore, our curriculum targets patients and their families. It will address the use of positive parental feeding practices [74,75] to promote healthy eating behaviors in children during and after cancer treatments, for example, healthy eating role modeling and avoidance of restrictions or control over eating [9,76].

The curriculum will put forward a positive and total diet approach to healthy eating that considers the whole eating pattern, suggests adding healthy foods instead of forbidding specific foods (apart from those restricted for food safety), and avoids categorization of food as “good” or “bad” [77]. The Mediterranean diet pattern is associated with the prevention of cardiovascular diseases [49] that are frequent long-term complications of CCS [4,5]. Therefore, coupled with Canadian Dietary Guidelines [78], this pattern has guided the development of nutrition education content and recipe criteria.

Food safety is a major concern during pediatric cancer treatment due to weakened immune system. It will be addressed throughout all cooking demonstrations when facilitators will model safe food handling practices. Only little evidence support a neutropenic diet to prevent infection for patients undergoing chemotherapy or radiotherapy, as the only few randomized control trials performed used variable methodologies and presented several limitations [79,80]. Indeed, a neutropenic diet may impose unnecessary food restrictions on patients who often consume insufficient dietary intakes [80,81].

### Considerations Related to Childhood Cancer

Further studies need to evaluate the feasibility of implementing workshops for pediatric oncology patients undergoing cancer treatments. The moment surrounding the diagnosis and treatment of cancer has been described as a *teachable moment* for a healthier lifestyle in adult cancer [82]. However, this opportunity window is not well documented in children. Families overwhelmed with the diagnosis might be less interested or find it too challenging to adopt healthy habits while experiencing a distressing life event [83]. However, focus groups with parents of overweight CCS testing a 6-lesson curriculum after completion of their child’s treatment revealed that some would have preferred to receive the intervention earlier in the process [67], supporting that the timing of our intervention might be optimal.

The heterogeneity of the target population, which comprises children of various ages, diagnoses, and treatments, was a challenge in the development of the curriculum. Evaluating the implementation of the workshops will inform us on participation rate and will allow to calculate sample size of future nutrition education and cooking program in pediatric oncology. The nonrandomized design is also a limitation of this study. Our study was designed to ensure that every newly diagnosed patient could participate and benefit from this novel lifestyle study. Therefore, control participants will only be recruited among patients who completed the standard treatment before the VIE Program was implemented.

We are confident that this intervention will contribute to increase knowledge about nutrition and cooking in the context of childhood cancer. Hopefully, it will improve children’s diet quality while promoting long-term healthy eating habits to prevent cardiometabolic complications. This research- and practice-based nutrition education and cooking demonstration curriculum will be a valuable complement to the VIE Program lifestyle intervention for the prevention of cardiometabolic long-term complications.

